#### Validation of the prediction model

The internal validation of the model will be performed using a bootstrapping method in the development cohort (n=657). A total of 500 samples will be generated and drawn randomly with replacement, and each sample will include the same number of patients in the development cohort. Moreover, the temporal validation will be conducted in the temporal validation cohort (n=281). The discrimination capability of the model will be assessed using the area under the receiver operating characteristic curve. Calibration of the model will be assessed using the Hosmer-Lemeshow goodness-of-fit statistic. The max-rescaled Brier score will be used to test the overall accuracy of the model. The clinical utility of the prediction model will be assessed using the decision curve analysis, and the results will be illustrated in a nomogram. Moreover, we will develop a web-based risk calculator by the shiny package to provide practical guide for clinic.

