#### Preoperative potential predictors

A total of 15 preoperative potential predictors:

Demographic data including age, gender and body mass index.ASA physical status.Comorbidities including hypertension, diabetes mellitus and the age-adjusted Charlson Comorbidity Index score.Autonomic nervous system function (assessed by symptoms and anamneses).^26 27^Myocardial injury (assessed by anamneses and preoperative examinations).Vital signs in the surgical ward including MAP and HR.Preoperative anxiety assessed by the first four items of the Amsterdam Preoperative Anxiety and Information Scale (APAIS).^28^Preoperative frailty evaluated with the FRAIL (fatigue, resistance, ambulation, illnesses, and loss of weight) scale.^29 30^Preoperative volume of fluid infusion and fasting duration.

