#### Intraoperative potential predictors

A total of eight intraoperative potential predictors:

Vital signs including MAP and HR immediately before anaesthesia induction.Dose of anaesthetics used for induction, including propofol, etomidate, ciprofol, esketamine, fentanyl and sufentanil.

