### Sample size estimation

According to previous literature,^5 8^ the incidence of PIH was approximately 35% for patients undergoing elective non-cardiac surgery. Considering a required number of 10 events per variable,^31–33^ we plan to recruit 657 patients for model development and internal validation (657=23×10/0.35). Another 281 patients will be included continuously for model temporal validation. Therefore, the planned sample size will be set to 938 patients.

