#### Development of the prediction model

The development cohort (n=657) will be used to construct the model. We will use the least absolute shrinkage and selection operator (LASSO) regression analysis for variable shrinkage and selection in the development of linear regression model. For centralisation and normalisation of variables, we will use the 10-fold cross-validation in the LASSO regression analysis, which will be repeated 10 times. In the 10 times 10-fold cross-validation, we will divide the development cohort into 10 equal parts. Then 9/10th of the data will be used to retrain the model and the remaining 1/10th will be used for validating the statistical accuracy in each time. The best lambda value will be selected. Based on the optimal predictors derived from the LASSO analysis, we will use the multivariable logistic regression analysis to develop a prediction model.

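### As described, the bootstrap validates an already selected model; unless LASSO selection is repeated in each resample, the internally validated AUC and Brier score will be optimistic

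*Protocol article*

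**What the plan says.** Development and internal validation are described as two successive steps.

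- **Development of the prediction model.** "The development cohort (n=657) will be used to construct the model". LASSO is run with 10-fold cross-validation, repeated 10 times, on that cohort. Then "The best lambda value will be selected", in the singular, and a multivariable logistic regression is built on the predictors that LASSO retains.
- **Validation of the prediction model.** "The internal validation of the model will be performed using a bootstrapping method in the development cohort (n=657"). There are 500 with-replacement samples, each as large as the development cohort. Temporal validation in 281 further patients follows.
- **Performance measures.** The validation section names the AUC, the Hosmer-Lemeshow statistic and the max-rescaled Brier score without tying them to one cohort. The Abstract ties discrimination, calibration and the Brier score to the temporal cohort.
- **Abstract and Discussion.** The Abstract assigns LASSO and logistic regression to development and bootstrapping to internal validation. The Discussion mentions the repeated cross-validation again and does not link it to the bootstrap.

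No section says that LASSO and the lambda search are rerun in each resample. None says that they are left out.

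**The concern.** An optimism bootstrap estimates how much a modelling procedure flatters itself on the data that produced it. It does this only for the steps that are rerun in each resample. If LASSO has already picked the predictors using all 657 patients and only the logistic coefficients are refitted, every resample inherits a predictor list that has already seen the original cohort. The part of the optimism due to selection is then not removed.

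Here 23 candidates face about 230 expected events, and the retained predictors enter a logistic regression for which no penalty is mentioned. On that reading the LASSO shrinkage is not carried into the final model. The bootstrap is then the main protection against overfitting within the development data. At stake is whether the internal figures published with the nomogram and web calculator are honest estimates for new patients of the same kind. A falsely high internal AUC could also make a lower temporal AUC look like a change over time.

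**Working it through.** **Inputs from the protocol article**

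- Candidates: "A total of 15 preoperative potential predictors" plus "A total of eight intraoperative potential predictors", so 15 + 8 = 23.
- Incidence: "the incidence of PIH was approximately 35% for patients undergoing elective non-cardiac surgery".
- Rule: "Considering a required number of 10 events per variable".
- Development cohort 657; 500 resamples of that size; temporal cohort 281.

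**The plan's own figure.** "we plan to recruit 657 patients for model development and internal validation (657=23×10/0.35"): 23 × 10 / 0.35 = 657.1, which reproduces 657. Expected events are 657 × 0.35 = 230. The plan states no figure for optimism, so its size has to be simulated.

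**Formula.** For each resample *b*, optimism(*b*) = AUC of model *b* in sample *b* minus AUC of model *b* in the original cohort. Corrected AUC = apparent AUC minus mean optimism. The question is whether model *b* uses the predictors already chosen (fixed) or is rebuilt from the 23 candidates (repeated).

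**Main simulation.** There were 60 data sets per scenario, n = 657, 23 candidates and about 35% events. Each data set had a logistic LASSO with 10-fold cross-validation at minimum deviance, then an unpenalised logistic refit, with 50 bootstrap resamples. True performance came from 60,000 new patients. Assumptions not in the documents: 8 true predictors and 15 noise variables, normally distributed, pairwise correlation 0.15, two signal strengths, minimum deviance as the meaning of best lambda, and a single rather than a 10-times repeated cross-validation.

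| | Stronger signal | Weaker signal |
|---|---|---|
| Mean number selected | 14.9 | 10.1 |
| Apparent AUC | 0.7537 | 0.6541 |
| True AUC | 0.7133 | 0.5958 |
| Corrected, selection fixed | 0.7287 | 0.6272 |
| Corrected, selection repeated | 0.7156 | 0.5977 |
| Bias, fixed | +0.0154 | +0.0314 |
| Bias, repeated | +0.0023 | +0.0019 |

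The Monte Carlo standard error of each bias is about 0.003 to 0.004. The fixed-minus-repeated difference is 0.0131 (SE 0.0006) and 0.0295 (SE 0.0016), well clear of simulation noise.

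**Second set of runs.** These used 40, 60 and 50 data sets with 40 resamples each, at true AUCs of about 0.71, 0.71 and 0.77. Their predictor structure and Monte Carlo error are not available, so they serve mainly to check direction.

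| Run | True optimism | Fixed | Repeated | AUC too high, fixed | AUC too high, repeated |
|---|---|---|---|---|---|
| 1 | 0.050 | 0.029 | 0.042 | 0.021 | 0.008 |
| 2 | 0.042 | 0.028 | 0.043 | 0.014 | −0.001 |
| 3 | 0.032 | 0.021 | 0.032 | 0.011 | 0.000 |

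**Share of the optimism missed with selection fixed.** Main simulation: 0.0154 / (0.7537 − 0.7133) = 38% and 0.0314 / (0.6541 − 0.5958) = 54%. Second set: 0.021/0.050 = 42%, 0.014/0.042 = 33% and 0.011/0.032 = 34%.

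Across all five scenarios, fixed selection leaves the AUC 0.011 to 0.031 too high. Repeating the selection leaves it within about 0.002 of the truth in four, and 0.008 too high in the fifth.

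**The case against.** **The text does not say that selection is held fixed.** This stands as a limit on the claim. Validating the model could mean validating its whole construction, LASSO included, and a condensed article may leave such detail to a fuller plan that is not shown. A reader might infer that the protocol commits to the wrong bootstrap and that its internal results are bound to be biased; the documents do not support that certainty. The objection does not dispose of the point, however. The article gives folds, repeats, the split, the number of resamples and their size. It places selection in the development step alone, with one lambda, and then bootstraps the result. The natural reading is the biased version.

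**Temporal validation guards against this.** True in part: performance in the 281 later patients is free of selection optimism however the bootstrap is coded. But that cohort is too small to expose the internal bias. With 281 × 0.35 ≈ 98 events, 183 non-events and an assumed AUC of 0.71, the Hanley-McNeil formula gives a standard error of about 0.034. The 95% interval is about ±1.96 × 0.034 = ±0.066, wider than a bias of 0.01 to 0.03.

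**Selection may not be the main source of overfitting.** A reader might infer that it is. The simulations put it at 33% to 42% of the optimism in four scenarios and 54% in the weakest-signal one. Coefficient estimation is usually the larger part.

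**Harm through calibration slope or shrinkage.** A reader might add that the bootstrap slope would shrink the model too little. The plan mentions neither a calibration slope nor bootstrap-based shrinkage; its only named calibration measure is the Hosmer-Lemeshow statistic. That harm is not part of this point.

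**Conclusion.** The point holds in conditional form. Read and followed as written, the internal validation corrects for coefficient estimation but not for predictor selection, so the internally validated AUC and Brier score will be optimistic unless selection is repeated. For the AUC the excess is roughly 0.01 to 0.03. The direction is consistent in every scenario. The size rests on assumed signal strengths, predictor structure and lambda rule, none of which the documents give. For the Brier score the direction follows from the same argument; its size was not calculated. The bias is confined to the internal estimate. It is modest, and correcting it is a cheap improvement.

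**What to change.** State in the validation section that in each of the 500 resamples every modelling step is repeated: standardisation, the cross-validated choice of lambda, LASSO selection from all 23 candidates, and the final logistic fit. Evaluate each resulting model in its own resample and in the original cohort, average the differences, subtract that average from the apparent value, and report the optimism-corrected AUC and Brier score. If this is already intended, one sentence settles it.

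The cost is computer time and a slightly lower reported internal AUC. No further patients or data are needed, and the temporal validation is unchanged.

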**Methods and analysis:**

A total of 938 elderly surgical patients (n=657 for development and internal validation, n=281 for temporal validation) will be continuously recruited at The First Affiliated Hospital of Soochow University in Suzhou, China. The main outcome is PIH during the first 15 min after anaesthesia induction or before skin incision (whichever occurs first). We select candidate predictors based on published literature, professional knowledge and clinical expertise. For model development, we will use the least absolute shrinkage and selection operator regression analysis and multivariable logistic regression. For internal validation, we will apply the bootstrapping technique. After model development and internal validation, temporal validation will be conducted in patients recruited in another time period. We will use the discrimination, calibration and max-rescaled Brier score in the temporal validation cohort. Furthermore, the clinical utility of the prediction model will be assessed using the decision curve analysis, and the results will be presented in a nomogram and a web-based risk calculator.

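### The only calibration measure named is the Hosmer-Lemeshow statistic, which shows neither size nor direction of error and, with 281 validation patients, would often miss moderate miscalibration

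*Protocol article*

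**What the plan says.** In the protocol article, the section on validation of the prediction model gives each aspect of performance its own method. Discrimination is measured by the area under the ROC curve. For calibration the text is: "Calibration of the model will be assessed using the Hosmer-Lemeshow goodness-of-fit statistic". For overall performance it is: "The max-rescaled Brier score will be used to test the overall accuracy of the model". Clinical utility is assessed by decision curve analysis.

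The abstract places the assessment in the later cohort: "We will use the discrimination, calibration and max-rescaled Brier score in the temporal validation cohort". The size of that cohort comes from the sample size section, "Another 281 patients will be included continuously for model temporal validation", with no calculation behind it. The same section assumes that "the incidence of PIH was approximately 35% for patients undergoing elective non-cardiac surgery".

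The predicted risks are meant for use at the bedside: "we will develop a web-based risk calculator by the shiny package to provide practical guide for clinic".

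No section mentions a calibration slope, an intercept, an observed/expected ratio or a calibration plot. The number of risk groups, the degrees of freedom and the significance level of the Hosmer-Lemeshow test are not stated.

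**The concern.** A nomogram and a web calculator give each patient an absolute risk, and decision curve analysis applies thresholds to that risk. Users of either need to know whether a predicted 40% is really 40%, and if not, in which direction and by how much it is wrong. The Hosmer-Lemeshow statistic adds up squared differences between observed and expected events over risk groups. Squaring removes the sign, and the sum is reported against a chi-square distribution. This loss of size and direction occurs at any sample size.

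The plan also makes one kind of error plausible. LASSO selects the predictors, a multivariable logistic model is then built on them with no shrinkage stated for that step, and the development sample rests on 10 events per candidate predictor. Risks that are too extreme in new patients (a calibration slope below 1) are therefore worth looking for. The slope measures this directly; the named statistic does not separate it from other misfit.

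At stake is whether the validation can tell readers how far to trust the displayed risks, and whether the model needs recalibration before use.

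**Working it through.** **The plan's own figure.** The development size is 23 × 10 / 0.35 = 657.1, against 657 stated, so it reproduces. The article gives no power or precision figure for calibration or for n = 281. The value is close to a 70:30 split: 657 × 3/7 = 281.6.

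**Inputs from the document.** Validation n = 281 and incidence 35%, so expected events are 281 × 0.35 = 98.35, about 98.

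**Assumptions not in the document.** True AUC of 0.70, 0.75 or 0.80 with a normally distributed linear predictor; 10 equal-sized risk groups; two-sided 5% level; reference chi-square with 10 df (appropriate for new data) or 8 df (the development-data convention).

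**Formula.** H = Σ (O_g − E_g)² / [E_g(1 − E_g/n_g)] over the 10 groups. The sign of O_g − E_g is lost.

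**Hand check for a 5-point error in mean risk.**
- Shift in events: 281 × 0.05 = 14.05.
- Approximate SD of the event count: √(281 × 0.35 × 0.65) = √63.93 = 8.00.
- z = 14.05 / 8.00 = 1.76. A direct observed-versus-expected test has about 42% power.
- Hosmer-Lemeshow spreads the same signal (non-centrality 1.76² ≈ 3.09) over 10 df. With critical value 18.31, power is about 17%, so about 83% of such models pass. With the 8 df critical value of 15.51, power is about 29%, so about 71% pass.

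**Simulation** (8,000 validation cohorts of 281 per scenario; in the slope scenarios mean predicted risk is held at 35%). Share of models that pass Hosmer-Lemeshow, range over AUC 0.70 to 0.80:

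| True state | 10 df | 8 df |
|---|---|---|
| Perfectly calibrated | about 95% | about 89% |
| Slope 0.8 | 71-86% | 59-74% |
| Mean risk off by 5 points | 70-86% | 56-74% |
| Slope 0.7 | 38-66% | 26-52% |
| Mean risk off by 7 points | 43-70% | 30-54% |
| Slope 0.6 | 8-31% | 4-20% |
| Mean risk off by 10 points | 10-35% | 6-21% |

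A separate simulation with linear-predictor SD 0.75 to 1.25 gave 74-86% (slope 0.8) and 85-87% (5 points) with 10 df, and 61-76% and 73-75% with 8 df. Together the two runs give the rounded range of 55-87%.

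**What these slopes mean in risk terms.** At slope 0.8 the mean absolute error is about 3 percentage points, and one patient in ten is off by more than 5 to 6 points. At slope 0.6 the mean error is about 7 points.

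**What direct estimates would give at n = 281.**
- Calibration slope in a well-calibrated model: SE 0.14 to 0.19, so a 95% CI of about ±1.96 × 0.14 = ±0.27 to ±1.96 × 0.19 = ±0.37.
- Observed incidence: SE √(0.35 × 0.65 / 281) = 0.028, so a 95% CI of about ±5.6 points.
- Test of calibration-in-the-large: 44-56% power for a 5-point error, against 14-30% for Hosmer-Lemeshow with 10 df; 72-84% against 30-57% for a 7-point error.
- Slope test at slope 0.8: 27-42% power, against 15-29%.

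**The case against.** **Low power is mostly a matter of sample size.** A direct slope test at n = 281 would also miss a slope of 0.8 more often than not. This stands. The gain from the change is an estimate with an interval, not reliable detection, so the power argument is secondary to the missing size and direction.

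**The power figures rest on assumptions.** The article states no AUC, grouping, degrees of freedom or level. This stands too, and is why ranges are shown.

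**Other measures in the plan respond to miscalibration.** The max-rescaled Brier score and the decision curve both worsen when risks are wrong. They are a partial safeguard, but neither isolates calibration, and the article does not present either as a calibration measure.

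**The article is condensed.** It commits to TRIPOD reporting through a checklist that is not shown, and naming one statistic does not rule out a plot or a slope elsewhere. So their absence alone is not the fault. The point is that the article does fix a calibration measure, and fixes a poor one for this purpose.

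**Stronger readings that the text does not support.** A reader might infer that the test will usually pass any materially miscalibrated model. It will not: at slope 0.6 or a 10-point error, at most about 36% pass in these simulations. A reader might infer that the plan is likely to certify a miscalibrated model, but the article gives no pass/fail rule and does not say that a non-significant result means good calibration. A reader might also infer that the statistic will be computed on the fitted development data and so be optimistic. The article does not say this; the abstract places calibration in the temporal cohort.

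**Conclusion.** The point holds in this form. The one calibration measure that the article names is uninformative about the size and direction of error, in a study whose product is an absolute-risk calculator. That conclusion needs no assumptions beyond the text.

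The size of the secondary problem depends on the assumed AUC of about 0.70 to 0.80, 10 groups and a 5% level. Moderate miscalibration (slope 0.8, or mean risk off by 5 points) would pass in roughly 55-87% of validations, depending on degrees of freedom. At slope 0.7 or a 7-point error the result is near a coin-flip with 10 df. Gross miscalibration is mostly detected.

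This should be changed. It does not invalidate the design, and it needs no more patients or data.

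**What to change.** In the section on validation of the prediction model, replace the Hosmer-Lemeshow sentence. Name as the main calibration measures the calibration slope and calibration-in-the-large (observed/expected ratio), each with a 95% confidence interval, together with a smoothed calibration plot. Report them directly in the temporal cohort of 281, and optimism-corrected in the development cohort from the 500 bootstrap samples already planned. Keep Hosmer-Lemeshow as a supplementary figure at most, and state that it will not be used to conclude that calibration is good.

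The cost is about one sentence in the plan and slightly more analysis. The intervals will be wide (about ±0.3 to ±0.4 on the slope), and the reported calibration may look less favourable than a single non-significant p-value. The width should be shown, because it is the uncertainty that a cohort of this size carries.

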#### Software

All data will be analysed using the R software (V.4.2.2, www.R-project.org/) and the SPSS software (V.26.0, IBM SPSS, Chicago, Illinois, USA).

#### Patient and public involvement

Patients and/or the public were not involved in the design, or conduct, or reporting, or dissemination plans of this research.

## Discussion

In this prospective cohort study, we will establish a model to predict PIH occurrence in elderly patients who are scheduled for elective non-cardiac surgery. Based on the main risk factors identified, the model will illustrate their effects on PIH. The effectiveness of the model will be verified via internal and external validations. To facilitate clinical application, we will visualise the prediction model in a nomogram and a web-based risk calculator. The incidence of PIH, different factors and the comparison with the existing models will be discussed in detail according to the study results.

To date, there have been many studies on the risk factors of PIH. A prospective multicenter observational study analysed 661 adult subjects who underwent elective non-cardiac surgery under general anaesthesia.^8^ They found that the probability of PIH increased with age, type II diabetes mellitus, the severity of hypertension at the time of operating room arrival and the dose of propofol. In their study, the blood pressure was measured at a 5-min interval, which may result in missing of hypotension events. In our study, we set the measurement interval at every 1 min for a total duration of 15 min or before skin incision, which improves the ability to detect PIH. In addition, the baseline MAP values will be determined in the ward preoperatively to avoid possible impact by anxiety after entering the operating room.^34^ Although several PIH prediction models incorporating machine learning have been reported,^11–13^ their data were retrospectively collected with a limited number of patients.

In contrast, our study is based on a prospective cohort design. We select the candidate predictors based on published data, professional knowledge and clinical expertise, which ensures the feasibility and practicality in finalising the model. Regarding the APAIS score and FRAIL score, we will collect these two variables using the easy-to-use evaluation forms with good clinical practicality. Last, we will perform 10-fold cross-validation in the LASSO regression analysis and repeat it 10 times. According to the best lambda value, the optimal predictors will be derived from the LASSO analysis.^35^

